### Histology and immunohistochemistry analysis

Formalin fixed biopsies will then be embedded in wax. Sections (4 μm) will be stained using haematoxylin and eosin (H&E) and scanned on an Olympus VS-120 scanning microscope. Morphometry will be performed to generate measurements of villus height and crypt depth as has been our standard practice for many years and on which several publications are based.
^
8
^
^,^
^
41
^
^,^
^
42
^ Recently a histological scoring system for EE has been developed in which we were involved, and this will be applied to generate scores for villus architectural change, Brunner’s gland penetration, Paneth cell depletion, Goblet cell depletion, intra-epithelial lymphocytosis, and epithelial abnormalities.
^
43
^ The expression of PRRs will be assessed in separate histological sections of antibody-labelled duodenal biopsies via immunofluorescence microscopy.

### EE biomarker analysis

To characterise the sample sets fully, giving context to observed changes in the composition of the microbiota, biomarkers of EE (shown in
Table 5) will be quantified in plasma and stool aliquots via ELISA.

**Table 5. T5:** Plasma and faecal biomarkers of EE.

Marker	Sample type	Measure
1. Endotoxin-core antibody (EndoCab) IgG, IgM, and IgA	Plasma	Microbial translocation
2. Soluble (s)CD14	Plasma	Microbial translocation
3. LPS binding protein (LBP)	Plasma	Microbial translocation
4. sCD163	Plasma	Marker of systemic inflammation
6. C-reactive protein (CRP)	Plasma	Microbial translocation
7. Acid glycoprotein (AGP)	Plasma	Marker of systemic inflammation
8. Myeloperoxidase (MPO)	Stool	Intestinal Inflammation
9. Intestinal fatty acid binding protein (iFABP)	Plasma	Marker of epithelial damage

### Cell culture analysis

To evaluate the capacity of circulating microbial products in plasma and microbial PAMP content in stool to activate innate immune signalling (immunogenicity; an indicator of microbial translocation), plasma and faecal water aliquots from each participant will be co-cultured with THP-1 Dual reporter cells for NFkB and IRF3 (monocytic cell line; obtained from Invivogen), which provide a global indicator of PAMPs that can trigger immune cell activation via Toll like receptors, a major pathogen recognition receptors of the innate immune system. We will then screen samples for more specific PRR signalling activity using PRR-specific HEK293 reporter cells (obtained from Invivogen), focusing initially on TLR4 (the receptor for bacterial LPS/endotoxin) and TLR5 (receptor for bacterial flagellin), but expanding to and other PRRs if indicated by microbial metagenomics/microbiome analyses. For PRR-specific reporter HEK293 assays, we will conduct parallel cultures with HEK293 lacking the receptor of interest (HEK293-null cells) as a negative control.

To evaluate the functional effect of PAMPs and immune mediators present in plasma and stool on gut epithelial barrier integrity (transepithelial resistance, TEER), permeability, PRR and tight junction expression, and epithelial cell activation, we will add aliquots of plasma/faecal water separately to the basal/apical side of
*in vitro* models of the gut epithelial barrier. For the model epithelium we will use Caco-2 (cell line derived from the human colonic epithelium; obtained from American Type Culture Collection, ATCC, cultured in transwell inserts so that they have an apical side (equivalent to the epithelial side facing the gut lumen) and a basal side (equivalent to the epithelial side facing the lamina propria),
^
44
^ to recapitulate the polarity of the gut epithelium. PRR-specific inhibitors or antagonists and/or antibodies and filtered faecal water will be used in parallel experiments to attempt to disaggregate the effects of the specific PAMPs present in the stool samples. We will use these data to explore the relationship between immunogenicity (from THP-1 and HEK293 reporter assays) and functional impact of the sample on the epithelial barrier
*in vitro* (from Caco-2 transwell models). We hypothesise that samples from participants with more circulating immunogenic PAMPs will be associated with greater loss of barrier function
*in vitro*.

### Antibiotic analysis

In the 20 patients attending for routine colonoscopy (for diagnostic purposes) in Harare, using luminal fluid, antibiotic analysis will be carried out by NMR or SUERC by LC-MS.

### Statistical analysis plan

With the complexity of the data set from the techniques described above, the biostatistical framework will be generated in a data-dependent manner. Data from novel tools will be integrated with mucosal morphometry, lactulose permeation, and biomarkers in blood and stool. All data will be tested for normality using a Shapiro-Wilk test and transformed accordingly (normalisation, scaling, etc.). Both parametric and non-parametric tests will be used and both univariate and multivariate analysis will be performed on all datasets generated, as appropriate. For univariate tests, to control for type-I errors, multiple testing will be corrected for by applying the Hommel correction (for Family-Wise Error Rate) or Benjamini-Hochberg (for False Discovery Rate) as appropriate for mildly (positively) correlated variables, or Benjamini-Yekutieli or Storey-Tibshirani (both for False Discovery Rate) methods for highly (positively and inversely) correlated variables. For multivariate tests, data will first be split into training (modelling) and test (evaluation) sets prior to any procedures on the data such as centering, scaling, or other transformations. The predictive classification models will be calculated only on the training portions and evaluated (accuracy and/or F1-score) on the test portions, with hyperparameter tuning using cross-validation on the training data. When small sample sizes do not allow setting aside a completely independent test set, repeated cross-validation will be used to ensure the robustness of the models by calculating a multitude of models (e.g. 1,000 individual models). The evaluation of performance is estimated across all models on the portion of the data that was set aside (test) in each partition. Where algorithms use random initializations of parameters, for each analysis the starting random number seed is saved to allow replication. All data generated will be compared with all duodenal morphometry data which is the most direct measure of EE severity; these comparisons will allow for validation of new real-team assessment tools and established laboratory techniques for sensitivity to differences in EE severity within the cohort.

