### Study strengths and limitations

•A study of 80 adults with EE and 20 controls will develop novel analytical tools to demonstrate their viability and effectiveness for the assessment of gut functional capacity compared with current ‘gold standards’.•This study will inform future work on EE disease assessment and in treating children with severe acute malnutrition (SAM) and/or stunting.•These novel tools will have practical applications in clinical assessments not only in EE but other conditions that affect gut functional capacity allowing better understanding of the underlying mechanisms of different diseases.•A limitation of this study is the lack of country-specific controls in whom the same assays would be performed for comparison.•Including adults only in this study limits the applicability of some of the analytical methods when designing a child-based study due to smaller sample volumes.•The data will be generated over the course of a single 3-day protocol; analysis of longitudinal changes will require additional studies.

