### Sample size estimation

As there are no, or very limited, data on these measurements in this population, the study was powered based on previous studies using stable isotope breath tests and permeability studies. Previous data from an enteropathy vs. healthy child cohort and
^13^C-sucrose breath tests
^
33
^ has suggested that calculating the cumulative
^13^CO
_2_ excretion, % relative to the dose, at 90 minutes post-intake best represents the villus integrity and the absorption capacity of only the small intestine. Preliminary data have shown that in a group of adults from Misisi with demonstrable sucrase-isomaltase (SI) expression in biopsies,
^
34
^ the mean cumulative % of dose excreted as
^13^CO
_2_ at 90 minutes is 20.29% compared to 16.02% in the group without SI expression, with SD of 5.29% – resulting in an effect size (ES) of 0.81.
^
34
^ With α = 0.05, power = (1-β) = 0.80 we estimate we need 20 samples per group for achieving 80% power with a one-tailed test. We will recruit 30 participants into the definitive studies, allowing for potential dropouts and incomplete sample sets. To estimate sample size for permeability studies we used data on circulating LPS concentrations in stunted children which were mean 481 EU/ml (SD 408) in Lusaka, compared to controls (mean 192, SD 113). This results in an effect size of 0.96, with α = 0.05 and power = 0.80 and we would require 18 in each group for a two-tailed test. The overall sample size was set at 80 adults to allow for sufficient power to cover a range of studies in adults and children.

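### Storey-Tibshirani is offered for highly correlated variables, where its false discovery rate control is not established; Benjamini-Yekutieli, offered beside it, should stand alone there

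*Protocol article*

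**What the plan says.** The rule is in the Statistical analysis plan section of the protocol article. Its purpose is given as "For univariate tests, to control for type-I errors, multiple testing will be corrected for". Two branches follow.

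- Mild correlation: Hommel for the family-wise error rate, or "Benjamini-Hochberg (for False Discovery Rate) as appropriate for mildly (positively) correlated variables".
- High correlation: "or Benjamini-Yekutieli or Storey-Tibshirani (both for False Discovery Rate) methods for highly (positively and inversely) correlated variables".

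The section states no false discovery rate level. The value 0.05 appears only under Sample size estimation ("α = 0.05, power = (1-β) = 0.80 we estimate we need 20 samples per group"). The scope is wide: "both univariate and multivariate analysis will be performed on all datasets generated, as appropriate". The section also says that all data will be compared with duodenal morphometry, as validation of the new tools.

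**The concern.** The two methods in the high-correlation branch have different guarantees. Benjamini-Yekutieli pays a fixed penalty and is valid under any dependence. Storey-Tibshirani estimates the share of true nulls from the p-value histogram and relaxes the threshold by that estimate. It relies on the histogram settling down as tests accumulate, which holds for independent or weakly dependent tests. A strong factor shared across a family moves many p-values together, so the histogram can look depleted of nulls by chance and the threshold is then relaxed too far.

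The plan therefore offers, specifically for high correlation, a method justified for weak correlation. NMR spectra, labelled amino acids, taxa and immune phenotypes can all be expected to contain correlated variables. False associations with morphometry could carry into the toolkit meant for later work in children. The two methods also differ greatly in strictness, so the choice between them can decide which tools are declared associated.

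**Working it through.** The plan gives no false discovery rate figure, so there is none to reproduce. The check compares the rules and then simulates them.

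**Inputs from the protocol article.** Group sizes of 80 and 20 ("A study of 80 adults with EE and 20 controls will develop novel analytical tools"); the two branches above; comparison of all data with morphometry.

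**Assumed inputs.** Level 5%, borrowed from the sample size alpha. Family size m, share of true nulls, correlation ρ (with random signs) and effect size are not in the article, so ranges are shown.

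**Rules.** Sort the p-values and find the largest k with p(k) ≤ k × 0.05 / (m × c). The methods differ only in c:
- Benjamini-Hochberg (BH): c = 1.
- Benjamini-Yekutieli (BY): c = 1 + 1/2 + … + 1/m. For m = 200 this is about 5.88, so BY acts like BH at 0.05 / 5.88 = 0.0085.
- Storey-Tibshirani (ST): c = the estimated null share, smoothed from #{p ≥ λ} / (m(1 − λ)) over λ = 0.05 to 0.95. If the estimate falls by chance to 0.5, ST acts like BH at 0.05 / 0.5 = 0.10.

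**Simulation 1.** t-tests of 20 versus 80, effect 0.9 SD, 2,000 replicates, spline smoother with 3 df. A null-share estimate at or below zero was reset to 1, which favours ST. Realised false discovery rate in %, for true-null shares of 100 / 90 / 50% (standard error at most 0.7 points):

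| m | Structure | ST | BH | BY |
|---|---|---|---|---|
| 200 | uncorrelated | 6.1 / 5.2 / 5.6 | 5.1 / 4.4 / 2.4 | 1.1 / 0.6 / 0.4 |
| 200 | one factor, ρ 0.5 | 8.6 / 9.0 / 7.8 | 3.0 / 3.5 / 2.2 | 0.6 / 0.6 / 0.3 |
| 200 | one factor, ρ 0.8 | 8.6 / 10.7 / 8.8 | 1.5 / 2.4 / 2.4 | 0.4 / 0.6 / 0.4 |
| 200 | blocks of 10, ρ 0.8 | 3.6 / 5.8 / 6.0 | 2.8 / 4.4 / 2.5 | 0.4 / 0.9 / 0.4 |
| 50 | uncorrelated | 7.2 / 7.5 / 8.3 | 5.4 / 4.9 / 2.4 | 1.5 / 1.0 / 0.6 |
| 50 | one factor, ρ 0.5 | 11.5 / 8.7 / 8.8 | 3.6 / 3.1 / 2.4 | 0.7 / 0.6 / 0.6 |
| 50 | one factor, ρ 0.8 | 5.9 / 6.6 / 7.5 | 2.0 / 2.3 / 2.1 | 0.6 / 0.5 / 0.4 |
| 50 | blocks of 10, ρ 0.8 | 6.5 / 8.7 / 9.1 | 2.8 / 4.2 / 2.2 | 0.4 / 1.1 / 0.5 |

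As a check on the code, BH without correlation should give 0.05 × the true-null share. At m = 200 and a share of 0.9 that is 4.5%, and the table shows 4.4%.

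For m = 50 in five blocks of 10, ST exceeds its own uncorrelated value by at most 8.7 − 7.5 = 1.2 points. In small families, then, most of the excess over 5% is estimator bias. In the one-factor rows at ρ 0.8 the null-share estimate was at or below zero in 18–24% of data sets. Resetting those to BH holds ST down, most visibly at m = 50.

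**Simulation 2.** 80 versus 20 t-tests, and correlations at n = 80 with a morphometry-like variable. ST gave 11–16% under one strong mixed-sign factor (m = 200), about 6–9% with five blocks at ρ 0.8, about 6–7% with ten blocks, and 5–7% without correlation. BH gave 2–4% and BY under 1%. A separate n = 80 correlation run (m = 200, one factor, ρ 0.8) gave ST 10–12% with a cubic smoother and 13–14% with λ fixed at 0.5.

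**Power.** About 28–57% for BY and 64–84% for ST. Where ST's false discovery rate is inflated, part of that gap is bought with the extra false discoveries.

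**The case against.** Several points on the other side stand.

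- The branch says one method or the other, and Benjamini-Yekutieli is listed first. A reader might infer that the plan has no valid control for correlated data. It does; only one of the two options is at fault.
- A reader might infer that a 5% rate promised by the plan is breached. The plan states no false discovery rate level, so 5% is an assumption.
- A reader might infer that the metabolite and taxon families will show large inflation. The documents give neither family sizes nor correlation structure. If dependence in those families is local, Storey-Tibshirani stays near nominal (3.5–6.0% with blocks of 10 at m = 200 to 1000). The highest figures, such as 12–24% in two blocks with no true effects, depend on extreme structures and on how null-share estimates at or below zero are handled. In the two-block case at ρ 0.9, resetting such estimates to 1 cut 21–24% to 14–16%.
- The null share is not usually far off. With five blocks at ρ 0.8 its median estimate was 0.74 against a true 0.80. The harm comes from a tail of data sets.
- A reader might conclude that Benjamini-Hochberg should be used throughout. It stayed at or below about 4% in the correlated runs, but it has no general guarantee under inverse correlation, and the plan rightly keeps it to mild positive correlation.
- The study is exploratory, and its predictive models are assessed on held-out or cross-validated data. Choosing one procedure per data type is commonly left to an analysis plan that is not shown, so the open choice alone is no finding.

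None of this defends Storey-Tibshirani in the high-correlation branch. That placement is stated, not omitted.

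**Conclusion.** The point holds as a wrong assignment within a stated rule. Storey-Tibshirani is offered for strong positive and inverse correlation, while its control is established only for independence or weak dependence.

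At an assumed 5% level the realised rate is about 11–16% under one strong shared factor, or about 9–11% for m = 200 at ρ 0.8 if unusable null-share estimates are conservatively reset to 1. It is about 6–9% with five large blocks and about 6–7% with many smaller blocks, where correlation adds little. The rate can exceed the nominal level; the documents do not show that it will. The figures rest on assumed family size, correlation structure, true-null share, effect size and null-share estimator.

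Severity is minor to moderate.

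**What to change.** Edit the multiplicity sentence as follows.

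- Delete Storey-Tibshirani from the highly correlated branch. Keep Benjamini-Yekutieli there, or name a permutation-based procedure that uses the observed correlation.
- Leave Benjamini-Hochberg for mildly positively correlated families, as written. It may be reported as a sensitivity analysis in the highly correlated families.
- State the false discovery rate level, and fix the procedure for each data type before results are seen.

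The drafting cost is about one sentence. The scientific cost is fewer discoveries in the highly correlated families, as the power figures above show. A permutation-based procedure may recover some of this, but that was not simulated here.

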### Study population

The initial study will be conducted in 80 adults from a population in Lusaka, Zambia, where our previous studies have demonstrated that EE is virtually ubiquitous in adults and children.
^
32
^ Additionally, 20 controls living in high socioeconomic status (SES) residential areas (Rhodes Park, Longacres, Kabulonga, Ibex Hill, Chelston, Avondale, Sunningdale, Roma, Chamba Valley, Lilayi, New Kasama and others) within Lusaka will be included. A further 20 patients attending for routine colonoscopy (for diagnostic purposes) in Harare, Zimbabwe will be enrolled for the antibiotic permeation study. As these participants will already be booked for colonoscopy they will be drawn from higher socio-economic groups.

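### Accuracy and/or F1-score are the only measures named for the classifiers; if the label is EE versus control (80:20), a rule with no discrimination outscores moderately good tests

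*Protocol article*

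**What the plan says.** The Statistical analysis plan section of the Protocol article sets out how multivariate models are built and judged. It states that "The predictive classification models will be calculated only on the training portions" and that they are then "evaluated (accuracy and/or F1-score) on the test portions". For small samples it adds that "When small sample sizes do not allow setting aside a completely independent test set, repeated cross-validation will be used". Under that scheme "The evaluation of performance is estimated across all models on the portion of the data that was set aside (test) in each partition", with no different measure named. The section does not mention sensitivity with specificity, AUROC, balanced accuracy, class weighting, stratified splitting or a no-information benchmark for the classifiers.

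On group sizes, Study strengths and limitations describes "A study of 80 adults with EE and 20 controls". Study population confirms that the controls are on top of the 80: "Additionally, 20 controls living in high socioeconomic status (SES) residential areas". The Lusaka total is therefore 100, with an EE share of 0.80.

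The article does not say which label the classifiers predict, which class counts as positive for F1, or how F1 is averaged. Separately, it plans to compare all data with duodenal morphometry, "for sensitivity to differences in EE severity within the cohort".

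**The concern.** Accuracy depends on the class mix, and at 4:1 it gives high marks to a model that ignores the smaller class. F1 behaves in the same way when the larger class is taken as positive. EE and control are the only two labelled groups recruited in Lusaka, so EE versus control is an obvious label for a classifier, and it is unbalanced by design.

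The study exists to find out which new tools measure gut function well enough to carry forward. If a classifier's worth is reported by these two measures alone, a score of about 0.8 to 0.9 could reflect nothing more than the recruitment ratio. A tool that does separate the groups could also look worse than one that does not. This is an objection to measures the article positively chooses, not to a detail left for a fuller plan.

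**Working it through.** The article gives no classifier performance figure, so there is none to reproduce. The check is direct arithmetic on the confusion matrix.

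**Inputs**
- 80 EE and 20 controls (Study strengths and limitations; Study population).
- Measures: accuracy and/or F1 (Statistical analysis plan).
- Assumptions not in the article: the label is EE versus control; EE is the positive class unless stated otherwise; the sensitivity (se) and specificity (sp) of the example tests, taken from a grid of 0.70 to 0.95.

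**Formulas**
- TP = 80·se, FN = 80 − TP, TN = 20·sp, FP = 20 − TN.
- Accuracy = (TP + TN)/100.
- F1 = 2TP/(2TP + FP + FN).
- Balanced accuracy = (se + sp)/2.

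**Results**

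| Rule or test (se/sp) | TP, FN, TN, FP | Accuracy | F1 (EE positive) | Balanced accuracy |
|---|---|---|---|---|
| Everyone EE (1/0) | 80, 0, 0, 20 | 0.80 | 160/180 = 0.889 | 0.50 |
| 0.75/0.90 | 60, 20, 18, 2 | 0.78 | 120/142 = 0.845 | 0.825 |
| 0.80/0.80 | 64, 16, 16, 4 | 0.80 | 128/148 = 0.865 | 0.80 |
| 0.80/0.90 | 64, 16, 18, 2 | 0.82 | 128/146 = 0.877 | 0.85 |
| 0.90/0.90 | 72, 8, 18, 2 | 0.90 | 144/154 = 0.935 | 0.90 |

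The 0.75/0.90 test loses to the trivial rule on both named measures. The 0.80/0.80 test ties on accuracy and loses on F1. The 0.80/0.90 test wins on accuracy and loses on F1, so the answer can turn on which side of the and/or is used. The 0.90/0.90 test wins on both. Balanced accuracy puts all four tests well above the trivial rule.

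**Where the crossover lies**
- Accuracy above 0.80 needs 80·se + 20·sp > 80, that is se > 1 − sp/4. This is 0.775 at sp 0.90 and 0.825 at sp 0.70.
- F1 above 8/9 needs 160·se/(80·se + 80 + 20(1 − sp)) > 8/9, that is se > 0.80 + 0.20(1 − sp). This is 0.82 at sp 0.90 and 0.86 at sp 0.70.

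**Sensitivity to the unstated choices**
- Controls as the positive class: F1 of the everyone-EE rule is 0, and its macro-averaged F1 is (0.889 + 0)/2 = 0.44. Its accuracy stays at 0.80.
- Even severity split within the 80 (40:40): the trivial rule gets accuracy 40/80 = 0.50 and F1 80/120 = 0.67.
- A test portion matches 80:20 only on average unless the split is stratified.

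**The case against.** The strongest reply is that the article never says that the classifiers separate EE from controls. The validation target it does name is morphometric severity within the cohort, and for a balanced severity split the distortion is much smaller. The F1 half of the point also needs EE as the positive class. Both objections stand, and they make the point conditional. They do not remove it: the accuracy problem for an EE-versus-control label does not depend on the positive class, and the morphometry comparison is a separate analysis that leaves the classifier measure unchanged.

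A reader might also infer more than the article supports:
- **That a useless tool could be reported as 80–89% accurate.** Its accuracy is 0.80; the 0.889 is F1, a different quantity.
- **That tuning rewards ignoring the controls.** The article attaches accuracy and F1 to evaluation on test portions. It says that tuning uses cross-validation on the training data but names no tuning measure.
- **That the hold-out default is itself an error.** The article already provides for repeated cross-validation when samples are too small for an independent test set, and gives no hold-out fraction from which to count the controls in a test portion.
- **That any useful test loses to the trivial rule.** Only tests of moderate sensitivity do, as the crossover values show.

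**Conclusion.** The point holds in conditional form. For any classifier of EE versus control in the 80:20 Lusaka sample, accuracy credits a rule with no discrimination with 0.80, and F1 credits it with 0.889 if EE is positive. That rule then ranks above moderately good tests, roughly those with sensitivity below 0.78 to 0.86 depending on specificity and measure. Strong tests are still recognised.

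The conclusion rests on the label being EE versus control and, for F1 only, on EE being the positive class; the article states neither. It does not show that tools will be shortlisted by these scores, only that the measures named are poor evidence of discrimination when the classes are this unequal.

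**What to change.** In the Statistical analysis plan section, amend the sentence on classifier evaluation so that, where class labels are unbalanced:
- AUROC and balanced accuracy (or the Matthews correlation coefficient) are the evaluation measures, reported with sensitivity and specificity and their confidence intervals;
- accuracy or F1, if shown, appears only beside its no-information value (for EE versus control, 0.80 for accuracy and 0.889 for F1 with EE positive; the reference for AUROC and balanced accuracy is 0.5);
- the class label and the positive class are stated for each model;
- splits or cross-validation folds are stratified by group.

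This needs no further participants, samples or assays, only a few lines of wording and minor analysis effort. The downside is that reported figures may look less favourable.

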## Discussion

Our project will take a holistic approach to understanding the impact of EE on gut functional capacity across the whole gastrointestinal tract, which means developing new tools for assessing multiple domains of physiology. This necessitates an assessment of the structure of the intestine (e.g., reduced villus height and therefore surface area, barrier function), digestive and absorptive capacity (e.g., enzyme activity for protein, fat and carbohydrate digestion, transporter expression for absorption), epithelial and immune responses to pathogens, PAMPs, and the microbiota, and the health of the gut microbiota and its metabolic activity. Through this study, we will be able to identify and select the combination of functional measures that are most sensitive to variations in gut physiology according to EE severity in this adult cohort. We will also be able to optimise protocols for communities, such as Misisi, where EE is the predominant gut phenotype. Such measurements will ultimately enable the design of novel therapeutic feeds which actively promote improved gut functional capacity, providing a novel approach to accelerate sustained rehabilitation, reduce mortality, and feed the superorganism (i.e., the host and microbiome), thereby improving growth in malnourished children.
^
21
^
^,^
^
28
^ The urgent problem which we aim to address in this proposal is the dearth of investigative tools available to measure these pathophysiological domains. These tools will be essential for the effective evaluation of new therapeutic feeds to be trialled in SAM and, critically, the selection of those that promote the healing of underlying defects as well as weight gain. Their application to childhood malnutrition will be highly original especially when linked to a clinical trial addressing patient-centred outcomes. Our research group will go on to conduct longitudinal studies and/or clinical trials to evaluate further the tools we will develop. This will provide a deeper understanding of the changing physiology and will generate essential data to support the findings of the trial. In the scenario where no benefit of a novel therapeutic intervention or feed is shown, our novel tools may provide essential for future refinements of the feeds to target specific domains of gut functional capacity and/or enhance effects on pathways showing positive sub-clinical modifications.

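### Refitting about 1,000 models on the same participants cannot secure the robustness claimed: it reduces partition noise only, and gives neither participant-level uncertainty nor the score of an uninformative tool

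*Protocol article*

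**What the plan says.** The Statistical analysis plan section of the protocol article sets up predictive classification models. By default, "data will first be split into training (modelling) and test (evaluation) sets prior to any procedures on the data", and the models are then "evaluated (accuracy and/or F1-score) on the test portions, with hyperparameter tuning using cross-validation on the training data". A fallback follows: "When small sample sizes do not allow setting aside a completely independent test set", the article says that "repeated cross-validation will be used to ensure the robustness of the models by calculating a multitude of models (e.g. 1,000 individual models"). On reporting it adds: "The evaluation of performance is estimated across all models on the portion of the data that was set aside (test) in each partition".

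The section closes by comparing all data with duodenal morphometry, so that new tools and existing methods can be validated, the latter described as "established laboratory techniques for sensitivity to differences in EE severity within the cohort". The Discussion expects that "we will be able to identify and select the combination of functional measures that are most sensitive to variations in gut physiology". On size, Study strengths and limitations states: "A study of 80 adults with EE and 20 controls will develop novel analytical tools". The Sample size estimation section works with 20 and 18 per group and mentions 30 participants for the definitive studies.

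**The concern.** The question for a classifier is whether a tool carries information about EE status or severity in people. The fallback answers a narrower one: how much the result changes when the same people are partitioned differently. The models share nearly all their data, so a stable average over 1,000 of them is compatible with a tool that has no information at all.

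The article nevertheless presents the number of models as what secures robustness. It reports raw accuracy and/or F1, whose no-information values are high when one group is four times the size of the other. At these sample sizes the fallback is likely to be used. A reader of the results could then take a narrow spread, or an accuracy that looks high, as evidence that a tool works.

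**Working it through.** **Inputs from the article.** About 1,000 models; accuracy and/or F1; 80 EE and 20 controls; 30 in the definitive studies; 20 and 18 per group.

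**The article's own figures.** It gives no figure for classifier precision. Its group sizes, used here only to set realistic n, reproduce by two-sample t-test at 80% power:
- Breath test: (20.29 − 16.02)/5.29 = 0.807, giving 19.7, so 20 per group (one-tailed).
- LPS: (481 − 192)/√((408² + 113²)/2) = 289/299.4 = 0.965, giving 17.9, so 18 per group (two-tailed).

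**Assumed, not in the article.** 1, 5 or 10 independent features unrelated to class; linear discriminant with equal priors; balanced accuracy, so chance is 0.50; either 1,000 random splits holding out 20% of each class, or 5-fold cross-validation repeated 200 times. The 40 vs 40 setting stands for 80 adults split into two severity halves. Each setting has 1,000 null datasets.

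**Formula.** Roughly, variance of the averaged performance = variance between participant samples + partition variance/number of models. Only the second term falls as models are added. The standard error over models is SD over models/√1000. For 20 vs 20 with 5 features this is 0.154/31.6 = 0.0049, while the SD of the average between null datasets is 0.083 to 0.085, and 0.083/0.0049 = 17.

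**Results** (ranges over the two schemes):

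| Groups, features | SD between datasets | SE over 1,000 models | Null 95th percentile | SE interval wholly above 0.50 | Repeat-mean range wholly above 0.50 |
|---|---|---|---|---|---|
| 15 vs 15, 5 | 0.092–0.093 | 0.0056 | 0.650–0.663 | 46–50% | 11% |
| 20 vs 20, 1 | 0.083–0.085 | 0.0048 | 0.647–0.655 | 43–45% | 18% |
| 20 vs 20, 5 | 0.083–0.085 | 0.0049 | 0.636–0.638 | 45–46% | 10% |
| 20 vs 20, 10 | 0.080 | 0.0049 | 0.625–0.629 | 45–46% | 7% |
| 40 vs 40, 5 | 0.059–0.060 | 0.0035 | 0.594–0.595 | 42–46% | 10% |
| 20 vs 80, 5 | 0.066–0.067 | 0.0038 | 0.612 | 47–50% | 15% |

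The last two columns have a nominal rate of 2.5%. The repeat-mean range is the central 95% of the 200 repeat averages (5-fold scheme only). If the central 95% of the 1,000 single-model accuracies is read instead, 0% of null datasets lie wholly above 0.50 in every setting, because small test folds make that range very wide.

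Mean null performance is 0.495 to 0.508, so there is no meaningful upward bias. A useless tool averages at least 0.60 in 14–17% of datasets at n=30, 10–16% at n=40, 4% at n=80 and 7–8% at n=100.

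**No-information values of the article's metrics** at 80 EE and 20 controls, labelling everyone EE (EE as the positive class): accuracy = 80/100 = 0.80; precision 0.80 and recall 1, so F1 = 2 × 0.80 × 1/1.80 = 0.89.

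**The case against.** Several points on the other side stand.

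- **The evaluation itself is sound.** Splitting precedes transformation and tuning stays within the training data. The simulation confirms that the averaged estimate is centred on chance for a useless tool.
- **Repeated cross-validation is a conditional fallback, not the only gauge.** The default is a separate test set. The section also has univariate tests with multiplicity correction, and it attaches validation to comparison with morphometry.
- **No decision rule is stated.** A reader might infer that a useless tool would be declared better than chance about half the time. That needs the standard error over models to serve as the yardstick, which the article never says. Other readings give 7–18% or 0%.
- **A reader might also infer that a false positive somewhere in Table 1 is almost certain.** The article does not say that each outcome gets a classifier or that all would use the fallback. The outcomes measured in Lusaka share participants, and the Aim 5 outcome is measured in separate Harare patients.
- **Selection on these figures is not stated.** The Discussion speaks of choosing sensitive measures, without naming classifier accuracy or a cut-off, and foresees further evaluation in later studies.
- **An article condenses the full plan.** A permutation comparison may exist elsewhere, and its absence here is not the point.

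It can also be said that robustness in repeated cross-validation simply means stability over partitions. If that is the intended meaning, the sentence should say so. As worded, it offers the number of models as an assurance about the models themselves, and re-splitting cannot deliver that.

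**Conclusion.** The concern holds as a defect in what the article claims for its method. Refitting on the same participants reduces partition noise only. Averaged performance keeps a participant-level SD of 0.06 to 0.07 at 80 to 100 participants and 0.08 to 0.09 at 30 to 40, about 17 times the standard error over 1,000 models. A balanced accuracy of about 0.59 to 0.61 at the larger sizes, or 0.63 to 0.66 at the smaller, is reached by a useless tool 5% of the time. On raw accuracy and F1, labelling everyone EE already scores 0.80 and 0.89.

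The simulated sizes depend on the assumed classifier, features and split; the principle does not. No single false-positive rate can be attached to the plan: it runs from 0% to about 50% according to how the spread is read, and the article leaves that open. This should be corrected. It does not show that the planned estimates are biased.

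**What to change.** In the Statistical analysis plan section, replace the stated purpose of repeated cross-validation with: *to reduce dependence on a single partition*. Then add text along these lines:

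*For each classifier, the labels will be permuted across participants and the complete pipeline (splitting, scaling, tuning, any selection of features or tools, repeated cross-validation) rerun, for example 200 to 1,000 times with fewer repeats per permutation. Performance, as balanced accuracy alongside accuracy and F1, will be reported against this null distribution, with the multiplicity correction of this plan applied across classifiers. The spread or standard error over the repeated models will not be used as the measure of uncertainty.*

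The smallest attainable permutation p-value is 1/(permutations + 1), so 200 permutations give 1/201 = 0.005. The upper end of the range is safer if many classifiers share the correction.

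The cost is wording and computing time; no participants, samples or procedures are added. The downside is that some modest performance figures will no longer count as evidence.
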